#### The intervention of usual care (control)

In this study, the usual care is access to public health and other treatment options that are available in the community. The CBS intervention is an intervention that takes place in Rwanda. They select people from the community (as described above) and assist them through the CBS intervention. Our research design aims to test the ecologically valid impact of the CBS intervention, meaning that we compare people who received the intervention versus people who are eligible for intervention (and were put on the waiting list). We opted for this approach as we could not create a meaningful intervention that could be used in the control group that would not generate a positive intervention effect (that would change the measures of our outcome variables). In addition, for ethical reasons, we did not want to engage the control group participants in placebo intervention activities that would not create a meaningful improvement in their lives.

#### Intervention description

The Community-Based Sociotherapy (CBS) intervention is one of the programs initiated in Rwanda to address the psychosocial needs of the Rwandan population in the aftermath of the 1994 genocide against the Tutsi and to restore the social fabric. CBS is a psychosocial peacebuilding intervention that has been shown to promote social cohesiveness, psychological well-being, reconciliation, and economic development among the populations of Rwanda [8, 19]. CBS is also evidenced in other conflict/post-conflict settings, including in the Democratic Republic of Congo [20] and Liberia [8].

In CBS, a group of 10 to 15 people gather in a circle to discuss their daily life problems and psychosocial distress, which turn out to often be related to their past and how it has affected their psychosocial health. The intervention is built on six consecutive phases, each focusing on a specific theme: safety, trust, care, respect, new life orientation, and memories. Throughout these phases, the following principles are applied: interest, equality, democracy, here and now, responsibility, active participation, and learning by doing [18] (see Fig. 1). In the sessions, the sociotherapy facilitators include exercises and cultural games and expressions, which contribute to cohesive group dynamics.

**Fig. 1 Fig1:**
[figure not shown]
Conceptual framework

The discussion of the psychosocial difficulties impacting both people and their community unfolds in particular over the course of the first four intervention phases, while the future life orientation and learning how to manage painful memories is the main focus of the final two intervention phases. The order in which safety, trust, care, and respect are established in the sociotherapy groups enables people to suspend the discussion of tough topics until an emotionally safe group environment has been created. Processing negative emotions takes place throughout the phases while in the sixth and final phase people are invited to focus on dealing with negative emotions in a constructive way as part of a new life orientation formation [8, 18, 26].

Every phase of sociotherapy is intended to advance the psychosocial health of the participants and their propensity to peaceful attitudes. The different phases help participants to not view life only in negative ways, but also to imagine and learn about establishing positive life experiences. The first phase, “safety”, provides a setting where each participant feels secure during group talks. In the second phase, “trust”, participants join together to rebuild the trust toward people and institutions lost by participants (perpetrators and survivors) following a history of trauma. Bringing social cohesiveness and psychological healing to each group member depends on re-establishing trust between cognitive and social-emotional attention and care for the individual inside the group [8, 26]. The third phase, “care”, is centered on people who had encountered bad experiences and had not been taken care of, had lost their ability to take care of themselves, or found it challenging to take care of others. In this phase, each participant grows sympathetic toward certain group members, the group dynamics come to life, and the group now serves as a conduit for social events [27]. In the fourth phase of “respect”, participants discuss how they were not respected and were prevented from respecting others due to various causes that negatively impacted their psychosocial well-being. Respect must be rebuilt inside the group, and each group member goes through the process of building self-confidence and fostering one’s dignity in relation to that of others [26]. In the fifth phase, “new life orientation,” participants compare their behaviors, feelings, and emotions before group sessions, as well as the benefits of group participation and their renewed emphasis on improving their psychosocial health. In the sixth and final phase, “memories,” individuals recall past traumas and relive the emotions that broke their lives’ equilibrium and relations with others. Participants recreate new meanings of their experiences after recalling both positive and negative situations [26, 27].

Since the start of the intervention of CBS, the implementation has gone hand in hand with monitoring, evaluation, and research activities for effective and evidence-based planning. Studies conducted on the CBS intervention demonstrated the effectiveness of the intervention in contributing to improved mental well-being, social connections, healing and reconciliation, social capital, reduction of partner violence, active civic participation, improved economic development, and peacebuilding [18, 24]. It also increased levels of trust among people, who subsequently start grasping the benefits of social networks (social capital), like expanding skills, accessing information, and joining efforts for their development either at the family level (bonding) or the broader community level (bonding and bridging), [28, 29].

#### Criteria for discontinuing or modifying allocated interventions

Over the past 15 years that the CBS intervention has been used and researched, both through qualitative and quantitative work, we have amassed good evidence that the intervention does not cause harm. On an individual level, the trial participants assigned to the study intervention will be discontinued whenever the participants (1) request to withdraw from the study or (2) do not comply with the group rules and regulations during the first session (including secret keeping).

#### Strategies to improve adherence to interventions

Individual face-to-face follow up by CBS facilitators with participants encouraging them to adhere to the group sessions, and further encouragement during the group sessions are part of the normal CBS practice and will also be implemented during the study.

#### Relevant concomitant care permitted or prohibited during the trial

To the best of our knowledge, there is no concomitant intervention implemented in the catchment area of the Community-Based Sociotherapy. The participants will be allowed to join any intervention that may be created during the trial period without the need to ask for the permission of the CBS facilitators. To control for co-intervention bias, we will monitor whether individuals are taking part in similar group therapeutic interventions [30].

#### Provisions for post-trial care

There is no risk associated with participating in this study, except perhaps the risk of some discomfort that participants may feel as we ask questions about their personal life. Moreover, a team of clinical psychologists will provide psychological support in the intervention of emotional crises. No direct compensation will be allocated to participants. Participants in the control group are waitlisted and will be invited to join CBS groups in future post-study intervention cycles.

### Outcomes

#### Primary outcome measure

Following extensive qualitative work with the CBS experts, we defined the impact of the CBS intervention in an itemized way. After we searched the literature for concepts that relate to the lists of items and through iterative feedback working loops between CBS experts and the literature, we came up with a contextually developed definition of social dignity, which CBS experts recognized as an ecologically valid primary outcome measure for CBS.

All items of the self-designed social dignity scale will be summed up to form a total score that will be used to estimate the primary outcome before and after the CBS intervention (baseline, endline1, and endline2). Each item is scored on a 5-point Likert Scale ranging from 1 (never) to 5 (always). We believe that this sum will give a valid measure of social dignity, as qualitative work preceding the trial did not indicate that we should weigh any item of the questionnaire higher than the other.

#### Secondary outcome measures

Measured before and after the CBS intervention (baseline, endline1, and endline 2):Sociodemographic characteristics (age, sex, marital status, location, education, occupation, and social category) will be measured using a sociodemographic questionnaire.Personal well-being will be measured using the WHO (Five) Well-Being Index [31].Perceived social support will be measured using the Multidimensional Scale of Perceived Social Support [32]PTSD symptoms will be measured using the Posttraumatic Stress Disorder Checklist for DSM-5 with LEC for PCL-5 [33].Depression symptoms will be measured using the Patient Health Questionnaire (PHQ-9), [34].Attributed dignity will be measured using the Jacelon Attributed Dignity Scale [35].Perceived parental self-efficacy will be measured by the perceived parental self-efficacy scale [36].

### Data collection timeline

The schematic chart and study schedule are shown in Fig. 2 and Table 1.

**Fig. 2 Fig2:**
[figure not shown]
The schematic chart

**Table 1 Tab1:**
[figure not shown]
Study schedule

Note: shaded cells indicate the main activity and their corresponding study dates

### Sample size

The sample size was estimated based on pilot study results. As there was no similar previous study allowing to asses intraclass correlation, the authors of this study have conducted a pilot study on a sample of 559 people. The objectives of the pilot study were (1) to test the psychometric properties of the Social Dignity Scale and (2) to assess potential Intra-CBS groups correlation. The results from the pilot study revealed an intraclass correlation of 0.15. The targeted treatment effects were established in terms of clinical judgment, not through the pilot of data [37]. According to previous CBS experience, an average of 3 out of 15 participants in a CBS group dropout the intervention without achieving at least 11/15 required sessions. All enrolled CBS groups are facilitated to the end of the intervention. Considering an intraclass correlation coefficient, Rho = 0.15 and a standard Alpha = 0.05, an a priori power calculation using the Optimal Design Software [38] revealed that 80 CBS groups (40 control and 40 intervention) composed of 12 participants each group would make it possible to achieve the standard power of 0.80 while detecting a small Cohen’s *d* effect size of 0.3. The required total sample was then found to be 960 (i.e., 12 × 80) participants. However, assuming a minimalistic response rate of 96% according to a previous similar social study in Rwanda evidencing that it ranges from 96% [39] to 99.8% [40], we would need to recruit 1000 participants. To provide a buffer against potential attrition-related problems, at least 15 recruited beneficiaries of CBS that fulfil the inclusion criteria will be included in the study making the final sample size to recruit up to 1200 participants.

### Assignment of interventions: allocation

#### Sequence generation

The computer-generated randomization sequence numbers will be generated using the SPSS (Version 28.0) statistical software. Details of the procedure are described in the “Randomization” section.

#### Concealment mechanism

Participants will be randomized using the computer-generated randomization sequence numbers by the University of Rwanda Researchers. Allocation concealment will be ensured, as the researchers will not release the randomization code before the participants provide the consent forms to avoid the influence of knowledge of the group to which they will be allocated if they join the trial [41].

### Assignment of interventions: blinding

A detailed description of the blinding procedures is described in the “Randomization” section.

### Data collection and management

#### Plans for assessment and collection of outcomes

A team of 20 data collectors will be recruited and given a 3-day training on evaluation objectives, introduction to ethical considerations, the content of the questionnaire, and electronic data capture followed by practical sessions to ensure accurate, reliable, and consistent data collection. In addition to self-designed measures on social dignity and reconciliation, we will use standardized questionnaires on mental health and psychosocial wellbeing. The interviews will take about 45 min.

### Plans to promote participant retention and complete follow-up

No additional strategies will take place to improve retention and completion by participants in this trial, in keeping with the ecological design of this study.

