### Ethical issues

Ethical approval has been granted by the Institutional Review Board of the College of Medicine and Health Sciences at the University of Rwanda. The trial has been registered with ISRCTN (ISRCTN11199072, registered on April 2, 2022). Eligible participants will be informed about this trial and sign the consent forms before participating in the study. The trained data collectors will obtain informed consent from trial participants invited by the CBS facilitators. To comply with ethical considerations, participants assigned to a waiting list (control groups) will participate in the intervention after the final evaluation exercise (nine months later). All data collected for the purpose of this study will remain confidential and accessible only to the research team. All information will be stored in a password-protected computer.

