## Discussion

This is the first study that evaluates the effectiveness of CBS on social dignity among its participants, including genocide perpetrators, survivors, their descendants, people in conflicts (family/community), and local leaders. This represents an ecologically valid approach as the primary outcome variable is the result of qualitative work with CBS experts which lead to the conclusion that this outcome best describes the true impact CBS intends to have (and drives secondary outcomes). Compelling evidence shows that CBS contributes to improved mental well-being, social connections, restorative justice, healing and reconciliation, increased trust and social capital, reduction of partner violence, active civic participation, improved economic development, and peacebuilding [28, 29, 49]. The proposed study will allow us to obtain a deeper understanding of the effectiveness of CBS on a psychometrically validated measure that reflects the functioning of CBS as understood by CBS experts, and will help us understand how this impact relates to secondary which are well-established and theoretically founded. Concretely, this study will allow us to measure the effectiveness of CBS among individuals dealing with the consequences of the 1994 genocide against the Tutsi on social dignity and related secondary outcomes. We hypothesize that participants in the intervention group will show improved social dignity and secondary outcomes compared to those in the control groups.

More broadly, this study could inform CBS implementers, policymakers, and other stakeholders and practitioners on the role of social dignity in interventions that focus on psychosocial healing interventions.

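### The ecological rationale may justify not pressing session attendance, but not declining extra effort to obtain endline outcome data (low severity, small wording change)

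*Protocol article*

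**What the plan says.** The section *Plans to promote participant retention and complete follow-up* consists of one sentence: "No additional strategies will take place to improve retention and completion by participants in this trial, in keeping with the ecological design" of the study. It is a stated decision with a stated reason, not a detail left to a fuller document.

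The ecological idea appears in three other places:
- In the section on usual care it describes the comparison: "Our research design aims to test the ecologically valid impact of the CBS intervention", set against eligible people on the waiting list.
- Under *Primary outcome measure* it describes social dignity, "which CBS experts recognized as an ecologically valid primary outcome measure for CBS".
- The *Discussion* repeats the outcome argument: "This represents an ecologically valid approach as the primary outcome variable is the result of qualitative work with CBS experts".

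Other relevant text:
- *Strategies to improve adherence to interventions* provides for "Individual face-to-face follow up by CBS facilitators with participants encouraging them to adhere to the group sessions" as part of normal CBS practice.
- *Ethical issues* says that "participants assigned to a waiting list (control groups) will participate in the intervention after the final evaluation exercise".
- *Plans for assessment and collection of outcomes* gives the interviews to 20 recruited and trained data collectors.
- *Primary analysis* is by intention to treat, on change to each endline, with the baseline score in the model.
- *Sample size* gives session dropout as 3 of 15 and, separately, plans by "assuming a minimalistic response rate of 96" per cent.
- The missing-data section states multiple imputation for missingness below 5%.

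**The concern.** One sentence covers two different things. Retention in CBS sessions is part of the programme under test, and leaving it at its natural level fits a trial of CBS as normally run. Completion of the endline surveys is part of the measurement. Pursuing someone for an interview changes neither what CBS delivers nor what the waitlist receives, so the ecological reason does not reach it.

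This matters because an intention-to-treat comparison needs outcomes from everyone randomised, and the two arms have different reasons to stay in contact. Facilitator follow-up about sessions can reach only the CBS arm while the trial runs. Controls are offered CBS once the final evaluation is done, which is a reason to remain. Endline loss could therefore differ by arm, in a direction that cannot be known in advance.

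The other safeguards do not replace follow-up. Recruiting 15 per group in place of 12 protects power, not against selective loss. Multiple imputation does not remove loss that depends on unseen outcomes, and it is stated only for missingness under 5%.

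**Working it through.** **1. The plan's own figures.** With 12 per group and ICC 0.15, the design effect is 1 + (12 − 1) × 0.15 = 2.65, so the effective size per arm is 480 / 2.65 = 181.1. For d = 0.3 and two-sided alpha 0.05 (sidedness assumed), power is 0.815 by the normal approximation and 0.805 by the noncentral t with 78 df, against the stated 0.80. Then 960 / 0.96 = 1000 and 80 × 15 = 1200. All stated figures reproduce.

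**2. Is power the issue?** No. By the noncentral t, 15 per group seen (no loss) gives 0.830, 14.4 per group (4% loss) gives 0.826 and 12 per group (20% loss) gives 0.805. Moving from 20% loss to complete follow-up adds 0.830 − 0.805 = 0.025. What remains is bias from unequal loss.

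**3. How many people.** Applying the 96% response rate to an endline, 4% of 1200 = 48 missing. The 5% imputation limit is 60, a margin of 12.

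**4. Size of the bias.** Suppose those lost score D SD lower at both baseline and endline, and let b be the slope on the baseline score. Losing a fraction f of an arm raises the mean of those seen by about f × D at both times. Baseline adjustment removes the share b. The shift in the arm difference is therefore

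shift = gap × D × (1 − b),

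where gap is the difference in the fraction lost between arms of 600. D = 0.2 to 0.5 and b = 0.3 to 0.7 are assumptions; the protocol gives neither.

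| Split of the 48 | Gap | Smallest shift (D 0.2, b 0.7) | Largest shift (D 0.5, b 0.3) | Share of 0.3 |
|---|---|---|---|---|
| 24 / 24 | 0 | 0 | 0 | about 0 |
| 36 / 12 | 6% − 2% = 0.04 | 0.04 × 0.2 × 0.3 = 0.002 | 0.04 × 0.5 × 0.7 = 0.014 | 1% to 5% |
| 48 / 0 | 8% − 0% = 0.08 | 0.08 × 0.2 × 0.3 = 0.005 | 0.08 × 0.5 × 0.7 = 0.028 | 2% to 9% |

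The sign depends on which arm loses more.

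**5. Check by simulation.** Settings: 40 groups of 15 per arm, ICC 0.15, no treatment effect, D = 0.5, change regressed on arm and baseline, 20,000 runs per setting. For b = 0.3, 0.5 and 0.7:
- the 36/12 split gives 0.014, 0.010 and 0.006 (formula the same);
- the 48/0 split gives 0.029, 0.019 and 0.012 (formula 0.028, 0.020 and 0.012);
- the 24/24 split gives 0.001, 0.000 and 0.001 (formula 0).

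The Monte Carlo standard error is 0.0005 to 0.0007.

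**6. Effort.** 48 people over 20 collectors is 2.4 each per endline. At an assumed three attempts per person, 144 attempts are needed, or 7.2 per collector.

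**The case against.** The strongest reply is that the sentence speaks of additional strategies. Read beside the adherence section, it may mean only that nothing beyond normal CBS practice will push people to complete the sessions. On that reading the ecological reason is sound. Intention to treat at both endlines already implies that everyone is to be interviewed, and at the planning figure of 4% missing the imputation rule applies.

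Much of this stands. The sentence is ambiguous, it covers both arms and creates no imbalance itself, and the bias is small. It does not remove the point, because the sentence sits under a complete follow-up heading, refers to completion in the trial, and as written rules out extra effort for outcome data too.

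A reader might go further and infer that people who leave CBS are not interviewed. With 20% lost in the CBS arm (3 of 15) against 4% of controls, the formula would give 0.16 × 0.2 × 0.3 = 0.010 to 0.16 × 0.5 × 0.7 = 0.056 SD, or 3% to 19% of the target. The protocol does not support that inference. It gives session dropout and survey response as separate figures and nowhere says that people who stop sessions go unsurveyed.

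Nor does the discontinuation section carry the inference. It says "the trial participants assigned to the study intervention will be discontinued whenever the participants (1) request to withdraw from the study", which is loosely worded, but its heading limits it to the allocated intervention.

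It is also fair that the protocol gives no costs, and that the attempt count leaves out travel across ten districts.

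**Conclusion.** The point holds as a low-severity design improvement. The plan contains no wrong figure or contradiction here. The reason given supports leaving session attendance alone but does not support forgoing effort to obtain endline outcomes.

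The expected gain is modest: protection against a shift of about 1% to 5% of the targeted 0.3 SD if the 48 expected losses split 36/12, up to 9% if all fall in one arm, and about zero if they balance. These sizes rest on three assumptions: that the 96% response rate applies to each endline, that those lost score 0.2 to 0.5 SD lower, and that the baseline slope is 0.3 to 0.7. How much of the shift extra contact attempts would remove has not been estimated.

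**What to change.** Limit the retention sentence to session attendance: no encouragement to attend beyond normal CBS practice. Add that the data collectors already planned will seek every randomised participant at both endlines, including those who stop CBS, with the same number of contact attempts in each arm, unless the person withdraws consent to data collection.

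The cost is a short wording change plus contact attempts and travel for about 48 people per endline at 4% non-response. CBS delivery and the comparator are unchanged.

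Optionally, and outside this finding, the discontinuation section could say that its criteria end session attendance only.
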